## Abstract

Primary dysmenorrhea (PD) is a painful menstruation that can persist for the duration of a woman’s fertile life. Non-steroidal anti-inflammatory drugs, hormonal therapy, physiotherapy techniques, etc., are the main treatments. The main objective of this study is to evaluate the effectiveness of transcutaneous posterior tibial nerve stimulation (TTNS) in PD patients. The study will consist of a single-blind randomized clinical trial, parallel-assigned with two arms. Women with PD (18–43 years) with regular menstrual cycles and at least 4 points in VAS will be randomly divided into experimental (TTNS) and placebo (simulated stimulation) groups during 12 treatment sessions (1 session/week) and several follow-ups: monthly during treatment and 1, 3 and 6 months after. Maximum and mean pain intensity, pain duration, pain severity, number of anti-inflammatory drugs, quality of life, sleep quality, overall improvement, treatment satisfaction and secondary effects will be measured once a month every 6 months and at 3 and 6 months. The Student’s *t*-test for independent samples or the Mann–Whitney U test will be used. The literature shows effective physiotherapeutic techniques for PD in the short term, which do not act on causes and have limitations. The TTNS technique can be used in transcutaneous and percutaneous modalities, with similar effectiveness, but the transcutaneous causes less discomfort. TTNS modulates pain, and long-term benefits could be achieved at low cost and without patient discomfort.

## 1. Introduction

Primary dysmenorrhea (PD) is a painful menstruation that usually begins six to twelve months after menarche and can remain throughout the fertile life of women, and is generally associated with a normal ovulatory cycle and without pelvic pathology [1,2,3,4].

PD affects approximately between 45–95% of women; however, a high prevalence has been found in adolescents and young women (16–25 years old) [1,3,5]. It is estimated that approximately 10–25% of women will suffer very severe pain that prevents them from carrying out daily activities [2,6,7].

The current PD pathogenesis is mainly related to an excessive release of prostaglandins by the endometrium into menstrual fluid. Prostaglandin F2 alpha (PGF2α) and natural prostaglandin E2 (PGE2) induce vasoconstriction and contractions of the myometrium. High levels cause uterine hypercontractility that triggers hypoxia and endometrial mucosa ischemia. This uterine hypercontractility together with hypoxia and ischemia could be the cause of the cramp-like pain in PD. It also has associated systemic symptoms with vasopressin (uterine flow reduction), local factors (cervix stenosis) and, sometimes, psychological factors [2,3,6,8].

Primary dysmenorrhea is commonly described as cramping (cramping or spasmodic pain) or aching or dull aching (pain that is not severe but is insidious or continuous and generally difficult to describe or locate). The pain is commonly localized on the lower abdominal or suprapubic region, with or without radiation to the lower back, medial thigh or upper legs. It can start a few hours before or after menstrual bleeding onset, lasts approximately 48–72 h, and is most severe during the first or second day of menstruation [2,3,4,5,6,7,8]. In 50% of cases, women may suffer other associated symptoms like nausea, dizziness, vomiting, diarrhea, fatigue, headache, appetite loss, edema and a feeling of heaviness, insomnia, negative psychological effects and lipothymia due to hypotension [1,2,3,9]. In many cases, this situation causes school and work absenteeism and limits social, academic and sports activities [1,3,8,10]. Dysmenorrheic pain represents an immediate negative impact on quality of life, mood and sleep during menstruation compared to the pain-free follicular phase of women with PD and compared to the menstruation phase of women without pain [2,6].

Pharmacological treatment is based on non-steroidal anti-inflammatory drugs (NSAIDs) and hormonal regulation (oral contraception) [1,3]. These treatments are considered quite effective, but have negative effects (gastrointestinal, renal and cardiovascular) not tolerated by all patients [3,11,12].

In addition, there are various physiotherapy treatments for PD pain which do not appear to have adverse effects and are usually well tolerated by patients; they include transcutaneous electrical nerve stimulation therapy (TENS) [13,14,15], manual therapy [16,17], acupuncture [18,19], cryotherapy [20] and therapeutic exercise [4,21,22,23], which has shown positive results [24].

In recent years, a novel technique has emerged that could be aimed at the treatment of uterine hypercontractility, in addition to reducing pain. This technique is called transcutaneous posterior tibial nerve stimulation (TTNS), which consists of a peripheral neuromodulation where the posterior tibial nerve is electrically stimulated above the medial malleolus. This technique was first described by McGuire et al. in 1983 for incontinence treatment using two transcutaneous electrodes, one on each leg [25]. In 1999, Stoller adjusted this method to the percutaneous technique and placed the two electrodes on the same leg [26,27]. Since then, the technique (both transcutaneously and percutaneously) has been studied for urological conditions (overactive bladder [28,29] and fecal incontinence [30,31]) and gynecological pathologies (chronic pelvic pain [32,33,34]), with effective results in reducing symptoms and quality of life improvement.

The technique action mechanism in urological dysfunctions could be the modulation of reflex pathways, rebalancing the inhibitory and excitatory impulses that control bladder function at the spinal cord level [29,32]. Different theories have been considered: the stimulation of somatic fibers modulates/inhibits A-delta and C-afferent fibers, which will reduce pain sensation (gate theory); or endorphins increase at the spinal level and c-fos expression decreases in the central nervous system [32,35].

There are no specific studies that treat PD using TTNS in the literature. Physiotherapists have tools for chronic pain management and health promotion, having skills to perform PD interventions [3,21].

The posterior tibial nerve (L4–S3) has the same medullary levels as the hypogastric sympathetic plexus (L4–L5) and the pelvic parasympathetic plexus (S2–S4). Its stimulation produces impulse rebalancing in these centers, as is the case with the posterior tibialis relationship with the voiding centers [36,37]. Through that stimulation, uterine myometrium contractions are reduced; pain is alleviated by the decrease in uterine hypercontractility. This reduction in pain improves quality of life and sleep.

The main objective of this study is to verify whether posterior tibial nerve transcutaneous stimulation improves pain, quality of life and sleep deficiency in patients with PD in the short, medium and long term.

## 2. Materials and Methods

### 2.1. Objectives

#### 2.1.1. Main Objective

To prove the Effectiveness of TTNS Treatment for PD in the Short, Medium, and Long Term

#### 2.1.2. The Secondary Objectives Are

To evaluate TTNS effectiveness in reducing NSAIDs in the short term.To evaluate TTNS effectiveness in reducing pain in the short term.To evaluate TTNS effectiveness in improving the quality of life of women with PD in the short term.To evaluate TTNS effectiveness in improving sleep deficiency among women with PD in the short term.To confirm if any decrease in pain is maintained over time.To confirm if any improvement in quality of life is maintained over time.To confirm if any improvement in sleep deficiency is maintained over time.To evaluate patient satisfaction with the treatment.To explore adverse reactions arising from the treatment.

### 2.2. Hypothesis

#### 2.2.1. The General Hypothesis Is That

The Application of TTNS Results in Decreased Pain during Menstruation, and An Improvement in Quality of Life and Sleep Deficiency

#### 2.2.2. The Secondary Hypotheses Are That

TTNS influences the nerve centers producing a modulation of reflex pathways, thus rebalancing the inhibitory and excitatory impulses that control painful uterine afferents.TTNS modulates A-delta and C-afferent fibers, which reduces pain sensation in the short-medium term and is maintained 6 months after treatment.

### 2.3. Design and Setting

This is an experimental study, a single-blind randomized clinical trial with a parallel assignment study with 2 arms, which will be implemented in a physiotherapy center.

The study will consist of four parts:

First interview. The study characteristics will be explained to the participants in a 30-minute interview. A signed informed consent document and a filled-in medical history sheet will be required to participate. This medical history sheet will be filled out by the participant with the support of the researcher during this first interview. It will consist of the following sections: demographic characteristics, life habits, general medical history, gynecological history, obstetric history, menstrual history and history of menstrual pain.

Evaluation phase. Several questionnaires during two consecutive menstrual periods will be filled out. These questionnaires will be given to the participants at the first inter-view and they will have to self-administer them during the following two menstrual periods. The objective of this phase will be to know the baseline status of the participants with respect to the variables studied.

Intervention phase. Participants included in the study will be randomly assigned to two groups, an interventional and a control group, at a 1:1 ratio. Participants will not know which group they belong to. One session a week (12–30 min) will be conducted. Both groups will receive a symmetrical biphasic current in different leg locations. The stimulation will be performed transcutaneously through two/four electrodes at the leg. The technique shall be always painless, without harmful effects. Patients must fill in the questionnaires and on the last day of the treatment a treatment satisfaction scale will be requested. These questionnaires will be self-administered. The satisfaction and global improvement scales will be completed on the last day of treatment in the office, but on an individual basis, without the advice of the researcher. In addition, after each treatment session, participants will fill out a side-effect questionnaire.

Re-assessment phase. The same questionnaires will be filled in a month after treatment, and 3 and 6 months after the treatment ends. In addition, at the end of the 6-month follow-up period, patients will be asked to fill out the adverse effects questionnaire and the satisfaction and global improvement scales again. All these questionnaires will be self-administered.

### 2.4. Sample

It is estimated that the study will have a sample of 60 participants (Figure 1). 

The inclusion criteria for participant selection will be the following: women aged between 18 and 43 years, who have regular menstrual cycles (21–35 days) and who present between 4–10 points of the visual analogue scale (VAS) during half of their menstrual cycles per year and/or during their last three cycles for pain located at the suprapubic area, abdomen, lower lumbar area, perineum and/or medial side of the thighs in the first two days of their menstrual cycle.

The exclusion criteria established will be: women with an intrauterine device implanted or women with hormonal treatment; those diagnosed in the last 18 months of secondary dysmenorrhea by their gynecologist (endometriosis, ovarian cyst, etc.); abdominal or pelvic surgeries during the study or having given a birth in the last 6 months; presence of skin lesions such as scars, erosions, etc., on the upper-internal face of the ankles; pregnancies; and women who have pacemakers, uncorrected coagulopathies, severe comorbid disorder, cancer (in the last 5 years or currently), severe mental disorders or lower-extremity neuropathies and physiotherapy treatments for this pathology one month before the study onset.

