## 3. Discussion

Dysmenorrhea is currently postulated as one of the health problems that most affect the quality of life of women, with repercussions on their working life. In addition, physiotherapy is very present today and treatments are emerging with the aim of improving pain and the quality of life of patients with urogynecological complications [31,32,46].

There are numerous studies in the literature about physiotherapy treatments which try to relieve menstrual pain [13,14,16,17,21,22]. There is considerable heterogeneity in the studies published related to physiotherapeutic treatments, with studies referring to manual therapy techniques, thermotherapy, cryotherapy, neuromuscular taping, therapeutic exercise and different electrotherapy techniques. Within the interventions related to electrotherapy, where the presented technique would be encompassed, the most used technique is TENS [13,14,47]. These studies compared the use of TENS for 3 months with a control group in a population of nulliparous and multiparous women of childbearing age, a sample similar to the presented study. Only one of the studies [47] did not allow the use of contraceptives and the other two studies allowed the use of NSAIDs. In the present study, women who have not used contraceptives or have an IUD implanted will be included, since in this case it is considered that it would be difficult to discriminate which effects could be attributed to the medication and which to the treatment applied in the study. On the other hand, the intake of NSAIDs is considered appropriate since it is taken as an indicator of pain improvement. As for the measurement tools, the vast majority of studies take the VAS as a reference for pain assessment, and statistically significant differences were observed when comparing between groups in the short-term decrease in pain [13,14,47]. Furthermore, in the study by Hai-Yan et al. [13], a statistically significant decrease in NSAID intake was observed when comparing both groups. On the other hand, two of the studies [13,14] did not show statistically significant improvements in the experimental group with respect to quality of life. Long-term follow-up is not observed in the studies presented, which is essential to understand the duration of the effects of the technique.

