In these studies, middle-aged men and women with a diagnosis of chronic non-cyclic pelvic pain of more than 6 months’ duration, in which PD was not found, were included. Although PD is considered a chronic pelvic pain, it is necessary to differentiate it from other non-cyclical pathologies such as endometriosis, interstitial cystitis, etc. Most of the intervention groups consisted of 12 weeks of treatment at the rate of one 30 min session per week of percutaneous application, inserting the needle 3–6 cm cephalad from the medial and posterior malleolus to the tibia bone and with a neutral electrode placed in the same leg in the plantar arch of the foot, by unilateral application. Stimulation parameters of 20 Hz frequency and 200 µs pulse duration and intensity at the motor contraction threshold were used. In the present study, the same application modality will be used, although it was decided to perform it bilaterally in order to increase the therapeutic effects and by transcutaneous application. The technique has been used over time in two variants, transcutaneous (using surface electrodes) and percutaneous (using needles). Most studies have used the percutaneous modality, but other studies have demonstrated similar transcutaneous modality effectiveness, with a discomfort reduction that patients feel when being stimulated [48,49]. All studies have suggested improvement in short-term pain, assessed with the VAS and/or the SF-MPQ. Regarding quality of life, some studies have assessed it using the SF-36 questionnaire, finding positive changes in some domains for the experimental group in the short term. However only one study [35] conducted long-term follow-up, which suggested that the technique is still effective 6 months after the end of its application, which would lead to an improvement of pain in the medium-long term. This is an interesting aspect of the present study, in which a long-term follow-up will be carried out up to 6 months post-treatment.

Finally, no studies addressing the treatment of PD using this technique have been found.

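### The 18-month limit on the secondary-dysmenorrhea exclusion leaves women with an older known diagnosis eligible for a trial in primary dysmenorrhea

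*Protocol article*

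**What the plan says.** Section 2.4 sets out the eligibility list.

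- **Inclusion:** age 18 to 43, regular cycles of 21 to 35 days, a VAS score of 4 to 10 in a set share of recent cycles, and pain in named body areas in the first two days of the cycle.
- **Exclusion, secondary causes:** "those diagnosed in the last 18 months of secondary dysmenorrhea by their gynecologist", with endometriosis and ovarian cyst given as examples.
- **Exclusion, surgery and birth:** "abdominal or pelvic surgeries during the study or having given a birth in the last 6 months".

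Three other places say who the trial is for. The Abstract describes the participants as "Women with PD (18–43 years) with regular menstrual cycles and at least 4 points in VAS". Section 1 says that primary dysmenorrhea "is generally associated with a normal ovulatory cycle and without pelvic pathology". Section 3 compares the condition with other chronic pelvic pain and says that "it is necessary to differentiate it from other non-cyclical pathologies such as endometriosis, interstitial cystitis, etc".

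Section 2.3 says that a medical history sheet, with a section on gynecological history, is completed at the first interview. Two menstrual periods of baseline recording follow, and then randomisation at 1:1.

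**The concern.** The exclusion is tied to the date of the diagnosis, not to whether the woman has a secondary cause. The age of a diagnosis does not show that the condition has gone. Applied literally, the rule admits women already known to have the kind of pathology that the article's description of primary dysmenorrhea sets apart. A positive or negative result would then describe a mixture of primary and known secondary dysmenorrhea, while the stated conclusion would be about primary dysmenorrhea only.

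The surgery item raises a smaller, separate problem. An entry criterion should be decidable at entry, and surgery that happens during the study is not. If a site treated it as grounds to take a randomised woman out, the loss would depend on something that happened after allocation. Pelvic surgery could also be prompted by the pain being studied.

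**Working it through.** No figure in the article depends on this point, so the check is mainly a reading of the passages against each other.

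**Step 1. Does any listed rule catch an older diagnosis?** Take a woman of 30 with regular cycles, a VAS of 6 on the first two days of each period, and a gynecologist's diagnosis of endometriosis made 19 months ago.

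| Place | Result for this woman |
|---|---|
| 2.4 inclusion: age, cycle length, VAS, pain site and timing | All met |
| 2.4 exclusion: secondary dysmenorrhea | Not triggered, since 19 months is more than 18 |
| Other 2.4 exclusions (intrauterine device or hormones, skin lesions, pacemaker, cancer, neuropathy, etc.) | Not triggered by the diagnosis |
| 2.3 first interview | Diagnosis would be recorded, but no listed rule acts on it |
| Gynecological examination or confirmation of primary dysmenorrhea | None described |
| Abstract, Section 1, Section 3 | She is outside the population described |

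She is eligible under Section 2.4 and outside the population described elsewhere. The same holds for any diagnosis older than 18 months.

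**Step 2. When can the surgery rule be met?** Section 2.5.4 places the end of treatment at 5 months and the end of reassessment at 11 months. Section 2.3 puts two menstrual periods, about 2 months, before randomisation. Months after randomisation: 11 − 2 = 9. Share of the study period: 9/11 = 82%. Most of the time in which "abdominal or pelvic surgeries during the study" can occur therefore lies after allocation. Surgery before entry is not covered, because the 6-month look-back is attached to giving birth.

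**Step 3. Scale, purely illustrative.** The article gives 60 participants (30 per arm at 1:1) and p < 0.05. It gives no effect size, standard deviation or power. The following are assumptions: a two-sided test, 80% power at the outset, a share f of women with an older known diagnosis, and no benefit at all in those women. In the normal approximation:

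- Detectable difference: d = (1.960 + 0.842) × √(2/30) = 0.723 SD.
- Power with dilution: Φ(d(1 − f)√(30/2) − 1.960).

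| f | Women of 60 | Power |
|---|---|---|
| 0% | 0 | 80% |
| 5% | 3 | 76% |
| 10% | 6 | 71% |
| 20% | 12 | 61% |

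If such women respond as well as the others, there is no dilution and the power stays at 80%. The range therefore runs from no loss to the figures shown, and nothing in the article says where in it the trial lies.

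**The case against.** **The label and the other criteria may already do the job.** The Abstract restricts the trial to women with primary dysmenorrhea, and Section 2.4 asks for pain in the first two days of the cycle, while Section 3 classes endometriosis among non-cyclical conditions. This shows the intent but does not carry it out. Section 2.4 itself lists endometriosis as a cause of secondary dysmenorrhea, so the authors accept that it can present as menstrual pain, and such a woman can meet every inclusion criterion.

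**The look-back may be deliberate.** Ovarian cyst is one of the examples, and an old diagnosis need not mean present disease. The authors may also have meant that a gynecologist should have ruled out secondary causes within 18 months. The first point stands in part: a resolved condition need not exclude, and the clinical wording is for the investigators. The second meaning is not in the text, and if it was meant, the sentence needs correcting anyway. The Section 3 statement is made while comparing earlier studies and is not an eligibility rule, but it shows which distinction the authors consider necessary.

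**The surgery item may mean foreseen surgery.** That is possible, and the rule can partly act in the two baseline months. A reader might infer that randomised women who have surgery are withdrawn or dropped from the analysis. The article does not say so, and their handling may be set out in a full protocol or analysis plan not shown here. Only the wording of the criterion is open to criticism.

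**Intrauterine device.** A reader might also see a contradiction between Section 2.4, which excludes women with a device, and the Section 3 sentence "women who have not used contraceptives or have an IUD implanted will be included". The reason given in that sentence, the difficulty of separating the effects of medication from those of treatment, makes sense only if the negation covers both items. The sentence is clumsy but agrees with Section 2.4.

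**Conclusion.** The point holds for the 18-month limit. As written, Section 2.4 admits women with a known older diagnosis of secondary dysmenorrhea, contrary to the population described in the Abstract, Section 1 and Section 3. What is at stake is whether the result can be stated as a finding about primary dysmenorrhea.

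Its size is unknown. The power figures above rest on an assumed prevalence, complete non-response and an assumed 80% starting power, so they should not be quoted as an expected loss. Non-response is itself open to doubt, since Section 3 reports benefit of tibial nerve stimulation in chronic pelvic pain. A reader might infer bias between the arms, but none is shown: randomisation gives such women the same chance of either arm.

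The surgery item is a minor wording fault. Each woman removed would be 1/30 = 3.3% of an arm, and the article does not say that any would be removed.

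**What to change.** 1. Reconcile the secondary-dysmenorrhea exclusion in Section 2.4 with the Abstract, Section 1 and Section 3, so that a known, unresolved secondary cause excludes a woman whenever it was diagnosed. Check this on the gynecological history already taken at the first interview. The investigators should decide the exact clinical wording, including what counts as resolved.
2. Reword the surgery item as abdominal or pelvic surgery planned at the time of entry. State that a woman who has surgery after randomisation stays in her assigned arm for analysis. Whether her sessions continue is a clinical matter for the investigators.
3. If women have already been enrolled under the present wording, report how many had an older diagnosis, by arm.

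The cost is a short amendment with no new data collection. The downside is a slightly smaller recruitment pool, and Section 4 already says that the specific criteria could limit the sample size.

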However, many limitations have been found in the reviewed publications, with low methodological quality. Likewise, it is observed that the treatment techniques used in these studies have been proposed to combat pain secondary to the underlying pathology and not to the cause itself, obtaining short-term results [8,13,21].

Posterior tibial nerve stimulation has been studied as a treatment for chronic pelvic pain with beneficial results in reducing pain and improving quality of life [32,33,34,35], although the literature analyzed is scarce and samples observed in studies are very small. 

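### The physiotherapy exclusion misses recent tibial nerve stimulation given for other conditions, although the protocol expects its effect to last 6 months

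*Protocol article*

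**What the plan says.** **Physiotherapy.** Section 2.4 excludes women who had "physiotherapy treatments for this pathology one month before the study onset". The rule has two limits: the treatment must have been for dysmenorrhea, and it must fall in the month before onset.

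**Persistence.** Section 2.2.2 hypothesises that TTNS acts on nerve fibers, "which reduces pain sensation in the short-medium term and is maintained 6 months after treatment". Section 3 supports this with one study in chronic pelvic pain, which "suggested that the technique is still effective 6 months after the end of its application".

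**Other uses of the technique.** Section 1 lists overactive bladder, fecal incontinence and chronic pelvic pain as conditions in which tibial stimulation has been studied.

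**Blinding and analysis.** Section 2.3 says participants will not know their group. Sections 2.6.1 and 2.6.2 place active electrodes at both ankles and sham electrodes on the outer thigh of one leg. Outcomes are self-administered questionnaires. Section 2.8 plans a comparison between groups and also changes within each group.

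**Hormones and IUD.** Section 2.4 excludes "women with an intrauterine device implanted or women with hormonal treatment". Section 3 describes the same population as "women who have not used contraceptives or have an IUD implanted will be included".

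**The concern.** The exclusion is meant to keep earlier physiotherapy from colouring the trial's measurements. For the one treatment that the trial itself tests, it does so only if that treatment was given for dysmenorrhea. On the protocol's own hypothesis, tibial stimulation given for a bladder, bowel or pelvic pain condition would still be acting months later, and nothing in Section 2.4 keeps such a woman out.

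Two things are at stake. First, her baseline pain may be lowered by a fading earlier treatment, so her change from baseline mixes that fading with the effect of the allocated arm. Second, she has felt stimulation at the ankle. A thigh placement may tell her she is on sham, and an ankle placement that she is on active treatment. Pain, quality of life, sleep, global impression and satisfaction are all her own reports, so lost blinding can act on each of them.

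The hormone and IUD wording is a separate matter of consistency: one section reads as current use, the other as past use.

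**Working it through.** **1. Can residual effect reach the measurements?** The run-in is two menstrual periods (Section 2.3), taken here as two cycles of 21 to 35 days (Section 2.4), followed by 12 weekly sessions (84 days). One month is taken as 30 days and 6 months as about 182 days. Study onset is taken as the start of the run-in, which fits the 5- and 11-month visits (2 + 3 + 6 months).

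| Earlier treatment | Required gap | To first session | To end of treatment |
|---|---|---|---|
| Tibial stimulation, other condition | 0 days | 42 to 70 days | 126 to 154 days |
| Physiotherapy for dysmenorrhea | 30 days | 72 to 100 days | 156 to 184 days |

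In the first row both time points lie inside 182 days, so on the protocol's own hypothesis carry-over can span the baseline and the whole treatment phase. In the second row the effect would be ending by the end of treatment, even if the 6-month figure applied to those techniques.

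**2. Does the pain threshold screen these women out?** Not fully. The VAS 4 to 10 requirement may be met over half of the year's cycles and/or over the last three. A woman whose pain is temporarily reduced can qualify on yearly history.

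**3. What happens to the randomised contrast?** The documents give no effect size, SD or power for the sample of 60, so the stated size cannot be reproduced. For illustration, take 30 per arm, two-sided alpha 0.05 (sidedness assumed) and SD 1. The difference detectable with 80% power is (1.96 + 0.84) × √(2/30) = 0.72 SD. Let f be the share of women with live carry-over in each arm and c its size in SD. Both are assumed.

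*Additive carry-over.* It lowers both arm means by f × c, so the expected difference does not change. A simulation with f = 20% and c = 1 gave 0.724 SD against a target of 0.723. Only the SD grows, to √(1 + f(1 − f)c²).

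*Worst case.* Women with carry-over gain nothing from TTNS, and the contrast becomes (1 − f) × 0.72.

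| f | Power, additive, c = 0.5 | Power, additive, c = 1 | Contrast, worst case | Power, worst case |
|---|---|---|---|---|
| 5% | 79.5% | 78.2% | 0.69 SD | 75.9% |
| 10% | 79.1% | 76.5% | 0.65 SD | 71.3% |
| 20% | 78.4% | 73.9% | 0.58 SD | 61.1% |

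**4. What happens to within-group change?** If carry-over is present at baseline and gone at the later visit, mean improvement is understated in both arms by f × c: from 0.05 × 0.5 = 0.025 SD to 0.20 × 1 = 0.20 SD over the same assumed range.

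**5. Blinding.** No arithmetic applies. Knowledge of the usual electrode site is present before randomisation, but it works through the arm received, so balanced allocation does not cancel it.

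**6. Hormones and IUD.** Section 2.4 reads as current use; Section 3 reads as no use, with no time window. Taken literally, Section 3 could also be read as admitting women with an IUD, whom Section 2.4 excludes.

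**The case against.** Most of the counter-case is sound.

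- **Randomisation.** Allocation is 1:1 and the effect is judged between groups, so earlier exposure is balanced in expectation. A reader might infer that carry-over dilutes the contrast. Step 3 shows that this needs the further assumption that exposed women gain less from TTNS, which the documents do not address. This part of the objection stands.
- **Persistence is claimed for tibial stimulation only.** A reader might set the one-month rule against the 6-month effect and call the whole physiotherapy washout too short. Section 3 describes techniques used in earlier dysmenorrhea studies as addressing "pain secondary to the underlying pathology and not to the cause itself, obtaining short-term results". It also reports that "no studies addressing the treatment of PD using this technique have been found", so earlier physiotherapy for dysmenorrhea will rarely have been tibial stimulation. The objection stands.
- **Hormones.** No section says how long hormonal effects last, so carry-over from recently stopped treatment has no basis in the documents.
- **IUD wording.** In the Section 3 sentence the negation most naturally covers both items, and the reason that follows (effects could not be told apart from medication) shows that exclusion is meant. The IUD ambiguity is loose English; the difference between current and past use remains.
- **Rarity.** The pelvic pain studies described in Section 3 enrolled middle-aged men and women. Nothing shows that many women aged 18 to 43 with dysmenorrhea have had tibial stimulation. This limits the size of the problem but does not close the gap.
- **Condensed article.** Look-back details may sit in a fuller protocol. But Section 2.4 does state the scope of the physiotherapy exclusion, and that scope is what leaves the gap.

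**Conclusion.** The point holds as a minor one. As written, Section 2.4 admits women who recently had the trial's own type of stimulation for another condition, while Sections 2.2.2 and 3 expect or cite an effect lasting 6 months. The consequences that follow are extra variance, understated within-group improvement and a route to unblinding.

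Dilution of the randomised comparison is possible, not shown. Its size cannot be derived, because the documents give neither the share of such women nor the strength of any residual effect. The figures above are illustrations over assumed shares of 5% to 20%, and even the lower end may exceed what recruitment would yield. The conclusion also takes the protocol's persistence hypothesis at its word, and assumes that it extends to stimulation given for another indication. The blinding concern needs neither assumption.

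The documents do not support the inference that the one-month rule is too short for dysmenorrhea physiotherapy in general, or that recently stopped hormones contaminate the baseline.

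**What to change.** Extend the exclusion in Section 2.4 to previous posterior tibial nerve stimulation, transcutaneous or percutaneous, for any condition. Record it as one question on the medical history sheet already completed at the first interview. The cost is one line of amendment and a few lost candidates. Section 4 already warns that the strict criteria may limit recruitment, but a rule that touches so specific a treatment should add little to that.

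Separately, reconcile Sections 2.4 and 3 on hormonal treatment and IUDs, so that both state whether current or past use excludes and both clearly exclude women with an IUD if that is the intention. The sponsor should decide the rule; no hormone-free interval is proposed here. This costs only wording.
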